## Hypotheses and aims

The hypothesised sequence of change in the RISE study is that implementing a water-sensitive intervention in informal settlements leads to improved physical environments, which in turn results in reduced human exposure to pathogenic faecal contamination and flooding hazards, resulting in improved human and ecological health and well-being (figure 1). Specifically, we hypothesise that the intervention will reduce environmental contamination with human faeces. We further hypothesise that this will reduce residents’ exposure to gastrointestinal pathogens that cause diarrhoeal disease, poor gastrointestinal function and nutritional deficits, which particularly impacts young children living in informal settlement conditions, as well as reducing exposure to faecal sources of antimicrobial resistance (AMR) genes. Our hypotheses align with the planetary health approach,^14^ acknowledging the complex interplay between multiple factors which include health, environmental conditions, urbanisation, water and sanitation management, gender and socioeconomic equity, and climate change.

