### Aim 2: human health

Our second aim is to assess whether the intervention leads to improved physical health outcomes as a result of improved environmental conditions, as hypothesised above. Prevailing biophysical conditions in informal settlements are conducive to the spread of infectious diseases. Ample vector breeding sites and poor preventative practices lead to mosquito-borne diseases.^28 29^ Children suffer from diarrhoea and poor nutrition,^30 31^ with contaminated water and soil acting as a source for transmission of pathogens derived from animal, human and environmental origins.^32 33^ Antimicrobial-resistant infections are also a growing threat to human health globally,^34^ and inadequate faecal waste management leads to environmental contamination, which may promote transmission of multidrug-resistant pathogens between humans and the environment.^35 36^ Young children under the age of 5 living in these suboptimal conditions are at especially high risk for undernutrition, diarrhoea and poor growth and development. Further worsening their physical health is the high prevalence of environmental enteric dysfunction, a chronic inflammatory condition of the intestine, which is associated with poor absorption of nutrients, growth faltering and impaired response to live enteric vaccines.^37 38^

By designing and delivering decentralised infrastructure appropriate to and scalable within informal settlements, we aim to improve faecal sludge handling and reduce contact with faecal contamination in order to interrupt the connection between the human faecal stream and the environment. These impacts are expected to decrease children’s exposure to gastrointestinal pathogens, as detected by molecular methods in faecal samples, to decrease environmental enteric dysfunction and to decrease the abundance and diversity of AMR markers detected in children’s gastrointestinal tract. Flood mitigation and improved access within communities will further decrease human contact with the overall reservoir of environmental pathogens, and falling vector abundance may decrease mosquito-borne disease.

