### Description of the intervention

The water-sensitive approach to upgrading implemented in the RISE study integrates urban design and urban water cycle planning and management, focusing on water conservation and reducing environmental pollution by improving the quality of wastewater and stormwater prior to reuse or discharge to the environment. Implementation of water-sensitive infrastructure will be site-specific, co-designed with each community and adapted to the different biophysical and sociocultural conditions in each informal settlement. The intervention includes specific components collectively designed to reduce residents’ exposure to faecal contamination, requiring evaluation of critical faecal contamination and community exposure pathways at each site to determine optimal available technology solutions. Delivery of traditional approaches to water and sanitation services such as private toilets and hand basins are incorporated. Importantly, solutions also include installation of broader decentralised water infrastructure options to control and reduce the release of contaminated sewage and household greywater into the environment, improve flood mitigation, lower exposure to polluted environments within settlements through better access options and provide source water availability through rainwater harvesting and wastewater recycling.

Specific infrastructure options include (figure 3):

New integrated ‘wetpods’: these are comprised of a toilet, hand basin and rainwater tank.Toilet connections: pressure sewers and traditional collection and treatment systems (pipes, manholes, septic tanks and drains).Wastewater treatment: constructed wastewater treatment wetlands for black water,^48–50^ and biofilters and biofilter drains for grey water.^51–54^
Stormwater drainage and treatment: this includes resizing, reprofiling and formalising drains, and swales, rain gardens and constructed stormwater treatment wetlands and permeable paving.^55–58^;Water supply security: rainwater tanks and collection, connection to municipal water supply, water supply disinfection and protection of existing shallow well water supplies.Access roads, utility corridors, raised pathways;Flood management: including backflow prevention, minor localised spot-filling, minor terrain modification and flood protection walls.

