### Statistical analyses

Analyses will be by intention to treat. Descriptive statistics will report characteristics of settlements and of individuals by randomised arm. Estimation of the effects of the intervention for each outcome will use generalised estimating equations with an exchangeable correlation structure and robust standard errors clustered at settlement level, scaled with a small-sample degrees-of-freedom adjustment.^98^ Data from 6-month, 12-month, 18-month and 24-month follow-up visits will be included in the analysis and the intervention effect estimated for the 6-month follow-up timepoint for prevalence and mean number of gastrointestinal pathogens, and at 12-month follow-up for diversity and abundance of AMR markers and for intestinal inflammation markers. For binary and count outcomes, we will use a logarithmic link to estimate ratios of prevalence and mean counts, respectively; for continuous outcomes, the identity link will be used to estimate differences in means. All models will adjust for the baseline covariates, number of children under 5 years, flood risk category (see Randomisation section) and asset score. To enable temporal adjustment, indicator variables for seasonal patterns (eg, rainy vs dry), local rainfall data for each site and an indicator term for any major flood event at a particular settlement in a particular quarter will be included in the models. For households that drop out of the study, we will employ multiple imputation using imputation models that preserve the hierarchical data structure. Additional sensitivity analyses will exclude households who moved into the settlement postconstruction. There will be no adjustment to the p values for the assessment of multiple primary health outcomes; however, all findings will be fully reported and interpreted based on incremental evidence.

We will explore relationships between environmental changes and health outcomes by modelling health outcomes at 12-month, 18-month and 24-month postconstruction, using changes in environmental measures at 6-month, 12-month or 18-month postconstruction, respectively, as principal covariates. We will estimate these effects using generalised estimating equations with preconstruction health and environmental parameters as baseline covariates aggregated at settlement-level and will include interactions of environmental changes with the intervention for effect-modification assessment, together with adjustment for potential confounders.

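### The effect models adjust for settlement flood events after construction, which the works may themselves change, so they may estimate only part of the intention-to-treat effect

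*Protocol article*

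**What the plan says.** All of the following is in the protocol article.

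- **Analysis principle** (Statistical analyses): "Analyses will be by intention to treat".
- **Data** (same section): "Data from 6-month, 12-month, 18-month and 24-month follow-up visits will be included in the analysis".
- **Baseline adjustment** (same section): "All models will adjust for the baseline covariates, number of children under 5 years, flood risk category (see Randomisation section) and asset score".
- **Time-varying adjustment** (same section): "To enable temporal adjustment, indicator variables for seasonal patterns (eg, rainy vs dry), local rainfall data for each site" are added, and with them "an indicator term for any major flood event at a particular settlement in a particular quarter will be included in the models". The only stated reason is temporal adjustment. No effect model without the flood term is described.
- **Intervention** (Description of the intervention): flood management is one of seven listed groups of infrastructure, "including backflow prevention, minor localised spot-filling, minor terrain modification and flood protection walls". Resized and reprofiled drains appear under a separate item.
- **Theory of change** (Hypotheses and aims): the improved environment is expected to lead to "reduced human exposure to pathogenic faecal contamination and flooding hazards", and through that to better health. Aim 2 adds: "Flood mitigation and improved access within communities will further decrease human contact with the overall reservoir of environmental pathogens". The Limitations section also places reduced flooding impacts within the primary focus, as a means of reducing faecal exposure.

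**The concern.** A covariate belongs in a model for the effect of assignment if assignment cannot change it. Season, rainfall and the flood risk category fixed before randomisation meet that test. A flood recorded at a settlement in a follow-up quarter may not, because some of the works are meant to reduce flooding and its consequences there.

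If the works do alter recorded floods, holding floods fixed removes that route from the arm coefficient. What remains is the effect not passing through flooding. That is a different quantity from the total effect of being assigned the upgrade, which is what an intention-to-treat comparison is normally read as giving.

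There is a second risk. Conditioning on a consequence of the works can link arm to unmeasured causes of flooding. A settlement that floods despite the works may differ from a control settlement that floods. Depending on how those unmeasured causes relate to pathogens, the resulting bias could go either way.

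As written, the term enters the models for all three primary outcomes, in a trial of 24 settlements.

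**Working it through.** **1. Is the flood term affected by assignment?** Timing: it is specific to settlement and quarter, and the outcome data are from 6 to 24 months of follow-up, so it comes after randomisation. Pathway: the intervention description, Hypotheses and aims, and Aim 2 together run from works to less flooding or less exposure when it floods, and on to less pathogen contact. Definition: the article does not define a major flood event. Data collection mentions flood assessment with satellite imagery and household questions that cover flooding, but ties neither to the indicator. So it may be affected by assignment; the text does not settle whether it is.

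**2. The plan's own power figure (context only).** Inputs from Sample size: 12 settlements per arm, 30 children each, prevalence 25% against 15% (ratio 0.60), correlations 0.10 (same period), 0.067 (different periods) and 0.10 (same child). Assumed here: two-sided 5%, and the mean of four follow-ups adjusted for one baseline.

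- Within-period term: (1 + 29 × 0.10)/30 = 0.130
- Between-period term: (0.10 + 29 × 0.067)/30 = 0.068
- v = (0.130 + 3 × 0.068)/4 − 0.068²/0.130 = 0.0479
- SE = √[(0.25 × 0.75 + 0.15 × 0.85) × 0.0479/12] = 0.0355
- Power = Φ(0.10/0.0355 − 1.96) = 0.805

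This reproduces the stated 80%. A t reference with 22 degrees of freedom gives 0.772.

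**3. What adjustment for floods does to the ratio.** Let f₀ and f₁ be the shares of control and intervention settlement-quarters with a recorded major flood, and g the factor by which a flood multiplies prevalence. On the log-link scale:

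flood-path ratio = [1 + f₁(g − 1)] / [1 + f₀(g − 1)]; flood-adjusted ratio = total ratio / flood-path ratio.

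The total ratio is held at the design value of 0.60. The values of f₀, f₁ and g are assumptions; the documents give none.

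| f₀ → f₁ | g | Flood-path ratio | Flood-adjusted ratio |
|---|---|---|---|
| 50% → 50% | 1.5 | 1.000 | 0.60 |
| 20% → 10% | 1.5 | 1.05/1.10 = 0.955 | 0.63 |
| 25% → 12.5% | 1.5 | 1.0625/1.125 = 0.944 | 0.64 |
| 50% → 25% | 1.5 | 1.125/1.25 = 0.900 | 0.67 |
| 40% → 10% | 2.0 | 1.10/1.40 = 0.786 | 0.76 |
| 50% → 12.5% | 2.0 | 1.125/1.50 = 0.750 | 0.80 |

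In the 50% → 25% row, a true 40% reduction appears as 33%, and ln(0.900)/ln(0.60) = 21% of the log effect is removed. Smaller inputs give values between 0.60 and 0.63.

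**4. Simulation check.** A log-link exchangeable GEE was fitted to simulated data (24 settlements, four visits, 200 replicates), without and with the flood term:

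| f₀ → f₁ | g | Without | With |
|---|---|---|---|
| 50% → 50% | 1.5 | 0.61 | 0.61 |
| 25% → 12.5% | 1.5 | 0.61 | 0.64 |
| 50% → 25% | 1.5 | 0.59 | 0.65 |
| 50% → 12.5% | 2.0 | 0.60 | 0.80 |

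These agree with the algebra within simulation error. Floods were generated with no unmeasured cause shared with the outcome, so the simulation shows attenuation only. The second risk has not been quantified.

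**5. Power at the attenuated ratios (context only).** Putting the adjusted prevalence into the step 2 formula gives about 74% at 0.63, 36% at 0.76 and, for 0.80, Φ(0.05/√[(0.1875 + 0.16) × 0.0479/12] − 1.96) = Φ(−0.62), or 27%. These figures credit the flood term with no gain in precision, and they inherit the assumed flood inputs.

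**The case against.** The best defence is that a major flood event may be external. Much of the article speaks of making residents less vulnerable to flooding and reducing its impacts, not of stopping floods. Two of the listed flood works are described as minor. If the indicator records a river, tidal or regional event that local works cannot prevent, it blocks nothing, as the first row of each table shows. This stands as a limit on size. It does not clear the term, because flood protection walls, backflow prevention and drainage are also listed and nothing in the article ties the indicator to an external event.

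The authors also had a reason for the term. Study settings describes tidal inundation, coastal sites and fluvial flooding. A reader might infer that season and local rainfall already capture all the relevant timing, but the documents do not support that, and with 24 settlements a chance imbalance in external floods could matter. This stands, and it is why the fix includes a replacement option.

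Two stronger readings should be resisted:

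- **That the intervention is built to prevent floods, so the indicator is certainly a mediator.** The Abstract gives the primary aim as reducing exposure to faecal contamination; flood control is one component, with designs chosen site by site.
- **That the bias must run towards no effect.** Attenuation is expected if the works reduce floods and floods raise pathogen prevalence, but bias through unmeasured causes of flooding has no known direction.

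**Conclusion.** The concern holds in conditional form. The article commits all the intervention-effect models to a flood covariate measured after randomisation that, on the trial's own theory, the works may change. To the extent that they do, the primary estimates are of a partial effect and not of the intention-to-treat total effect.

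The size cannot be derived from the documents. It is zero if the works do not alter recorded major floods. Under the assumed flood frequencies and multipliers above, a true ratio of 0.60 could appear as about 0.63 to 0.80; the upper end needs frequent floods, a large cut in them and a doubling of prevalence. A reader might take one of the power figures as the expected loss, but the documents support no single figure, and the verdict does not rest on power.

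The case for changing the sentence does not depend on the size. If the works affect recorded floods, the term distorts the total effect. If they do not, leaving it out costs only some precision.

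**What to change.** Amend the sentence in Statistical analyses before outcome data are analysed, in one of two ways:

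1. Remove the settlement flood-event indicator from the primary effect models, keeping season, site rainfall and baseline flood risk category.
2. Replace it with an indicator of an external event that the works cannot alter, such as regional rainfall, river level or tide level, with its source and threshold defined in advance. This keeps adjustment for tidal and river flooding that season and site rainfall may miss.

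Under either option, report the model with the settlement flood-event term only as a labelled sensitivity or mediation analysis. The exploratory models already planned to link environmental change to later health outcomes are a natural place for it.

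Option 1 needs no new data. Its cost is a slight loss of precision if floods unrelated to the works explain outcome variance, and a chance imbalance in such floods would be left to the sensitivity analysis. Option 2 needs an external series for each city.

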## Study methods and analysis

### Overview of the study design and timeline

To evaluate the RISE intervention, we are conducting a cluster RCT involving 12 informal settlements in Suva, Fiji, and 12 in Makassar, Indonesia, with clustering at the settlement level. In each country, half of the sites have been randomised as intervention communities and will receive an early upgrade. The remaining communities will serve as controls and will receive only standard, basic hygiene and sanitation messages. Monitoring and assessment will be conducted in all settlements over an approximate 5-year timeline, which will include baseline data collection, the design and build implementation phase of the project, and 2 years of post-build monitoring (figure 2). After completion of the study, the intervention will be implemented in the 12 control settlements.

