### Randomisation

Randomisation was performed separately for each city: March 2019 in Makassar and November 2019 in Suva (figure 2). Randomisation occurred following settlement recruitment and completion of 12 months of baseline surveys. Settlements (clusters) have been randomly assigned to either intervention or control groups, with equal numbers in each group. Covariate-constrained randomisation was utilised using the cycrand package in Stata V.15 to achieve balance between the intervention and control groups on key baseline factors determined a priori.

For Makassar, intervention and control groups were first balanced on number of children aged under 5 years (four settlements in each group: ≤10, 11–30 and >30 children) and flood risk (high and low, six settlements in each), producing 90 allocations. Subsequently, the 30 allocations most imbalanced on average asset score were removed, with the score determined from each household’s ownership of selected assets. For Suva, intervention and control groups were first balanced on number of children aged under 5 years (<40 children, eight settlements; >40 children, four settlements) and flood risk and site contamination grouping (two extreme risk, two high risk, and eight medium risk settlements). This resulted in 120 allocations, from which the 30 most imbalanced allocations of asset score were removed, followed by the 30 most imbalanced allocations of average number of children under 5 years. For each of the cities, this resulted in the 60 best balanced allocations being used for the randomisation (total 3600 (60×60) possible allocations for the trial). A randomisation ceremony was held in both cities, where a child from the pilot community selected a ping pong ball from a large glass jar that contained 60 ping pong balls numbered 1–60, representing the 60 determined random allocations that achieved the balance criteria specified above.

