Laboratory technicians conducting sample analyses will be blinded to the intervention assignment throughout the study duration through the use of barcodes for sample identification. Owing to the nature of the intervention, community participants will not be blinded.

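### The in-migration sensitivity analysis cuts off at construction, about 2 years after an unblinded allocation, so most households that arrived after allocation stay in it; the date for control settlements is also not stated

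*Protocol article*

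**What the plan says.** The Statistical analyses section fixes the main approach, "Analyses will be by intention to treat", and then adds: "Additional sensitivity analyses will exclude households who moved into the settlement postconstruction". Because later arrivals are removed only in an additional analysis, the main analysis evidently keeps them. The article describes no other check on in-migration.

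The other relevant statements are:

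- **Time of allocation** (Randomisation): "March 2019 in Makassar and November 2019 in Suva". The same section says "Randomisation occurred following settlement recruitment and completion of 12 months of baseline surveys" and "A randomisation ceremony was held in both cities".
- **Blinding** (end of Statistical analyses): "community participants will not be blinded".
- **Control settlements** (Overview of the study design and timeline): "The remaining communities will serve as controls and will receive only standard, basic hygiene and sanitation messages". Their upgrade comes later: "After completion of the study, the intervention will be implemented in the 12 control settlements".
- **Timeline** (same section): about 5 years in total, made up of baseline, a design and build phase, and 2 years of monitoring after the build.

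**The concern.** An analysis that removes in-migrants from a cluster trial should show whether the result depends on people who chose their settlement knowing its allocation. The natural boundary is the date when allocation became known. Here the boundary is construction, which comes later. In between, residents of intervention settlements take part in co-design, so the coming upgrade is known locally. A household that moves in during that phase, or decides against it, may do so because of allocation, and the planned exclusion does not touch it.

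If main and sensitivity results agree, a reader may conclude that selective in-migration has been ruled out, when most of the arrivals who could be selective were in both analyses.

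A second, smaller gap is that control settlements have no construction within the trial and the article gives no equivalent date for them. Two analysts could apply the sentence differently.

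**Working it through.** The plan gives no figure for this point, so there is none to reproduce. The check is timeline arithmetic.

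**Inputs from the article**

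- Total timeline: about 5 years (Overview of the study design and timeline).
- Baseline before randomisation: 12 months (Randomisation).
- Monitoring after the build: 2 years (Overview).
- Pathogen effects are estimated at 6 months; antimicrobial resistance and inflammation effects at 12 months (Statistical analyses).
- About 55 dwellings per settlement (Sample size).

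**Step 1: gap between allocation and the end of construction**

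G = 5 − 1 − 2 = about 2 years. The total is approximate and the timeline figure is not shown, so G is varied from 1 to 3 years.

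**Step 2: share of post-allocation arrivals that the rule keeps**

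Assume a constant arrival rate. At time t after the build, arrivals since allocation are proportional to G + t, and those before the end of the build to G. The share kept is G / (G + t), whatever the rate.

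| Time after build | G = 1 year | G = 2 years | G = 3 years |
|---|---|---|---|
| 6 months | 1/1.5 = 67% | 2/2.5 = 80% | 3/3.5 = 86% |
| 12 months | 1/2 = 50% | 2/3 = 67% | 3/4 = 75% |
| 24 months | 1/3 = 33% | 2/4 = 50% | 3/5 = 60% |

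These shares hold for intervention settlements, and for controls if a matched calendar date is used.

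**Step 3: what a constant rate hides**

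If arrivals speed up once the infrastructure is finished, the share kept falls. As an assumed example, if the rate doubles after the build and G = 2, it is 2 / (2 + 2 × 0.5) = 67% at 6 months and 2 / (2 + 2 × 1) = 50% at 12 months.

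**Step 4: number of households**

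The article gives no in-migration rate. For assumed rates, with G = 2 and 55 dwellings:

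| Assumed annual rate | Arrive in the gap and are kept (55 × rate × 2) | Arrive by 6 months after the build and are removed (55 × rate × 0.5) |
|---|---|---|
| 2% | 2.2 | 0.6 |
| 5% | 5.5 | 1.4 |
| 10% | 11.0 | 2.8 |
| 15% | 16.5 | 4.1 |

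**Step 5: the control date**

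Read literally, no control household can meet the exclusion during the trial, because control construction follows completion. Yet the Sample size section times the between-arm contrast from construction, and Statistical analyses dates outcomes from construction without distinguishing arms. Controls must therefore have some reference date, or the comparison could not be run. The article does not say what it is or whether the exclusion uses it. Nor can it be inferred from the design: randomisation was covariate-constrained within city, not pair-matched, so no control settlement has a partner whose build date it would inherit.

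**The case against.** The strongest reply has four parts.

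1. **A matched control date is implied.** Postconstruction serves as a common clock for both arms, and a condensed article may leave the exact date to the full protocol or analysis plan. This stands. A reader might infer that the rule drops recent arrivals from the intervention arm only and so creates a bias of its own. The article does not establish that. Nor can such a bias be sized from it: that would need the share of arrivals and their prevalence relative to long-term residents, neither of which is given, and even its direction would depend on who moves in.
2. **The rule does remove some arrivals influenced by allocation.** Those who come after the build may be the ones most attracted by finished infrastructure. This also stands. It would be wrong to say that the check removes none of them; it misses those who came earlier.
3. **In-migration may be low.** The selection criteria require secure tenure and clear physical boundaries, and the Makassar sites are described as dense with little open space. This limits the absolute numbers, as the 2% row shows. It does not alter the share kept under a constant rate.
4. **This is only a sensitivity analysis.** No primary estimate, power figure or error rate depends on it, and a construction cut-off answers a legitimate, slightly different question. That is a reason to keep it, but not to leave it as the only check.

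What survives is the position of the cut-off. A matched calendar date would treat the arms alike but would still fall after allocation.

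**Conclusion.** The point holds in a limited form. On any reading, the exclusion keeps households that moved in between allocation and the end of construction. With a gap of about 2 years and a constant arrival rate, these are about 80% of post-allocation arrivals at 6 months and about 67% at 12 months; the ranges for gaps of 1 to 3 years are 67% to 86% and 50% to 75%. The shares rest on the approximate timeline and would be lower if arrivals accelerate after the build. The number of households depends on an in-migration rate that the article does not give.

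That residents knew the allocation is inferred from the ceremonies, the lack of blinding and the co-design process. The missing control date is an ambiguity to close. The planned check is weak evidence against selective in-migration; it is not shown to be biased, and the intention-to-treat result is unaffected. This is a cheap improvement.

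**What to change.** Add one sensitivity analysis restricted, in both arms, to households enrolled before randomisation in their city (March 2019 in Makassar, November 2019 in Suva). Define the set by household and keep children born into those households later. With a gap of about 2 years, the 24-month visit falls about 4 years after randomisation, so few children still under 5 would have been alive at allocation.

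Keep the postconstruction version as a second analysis, and state the calendar cut-off for controls, the same as that used for intervention settlements. If builds finish at different times within a city, say how the control date is derived.

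The cost is a sentence or two and no new data collection. Recruitment was attempted for all households within each boundary and, with 12 months of baseline surveys, preceded randomisation, so enrolment records should identify the set in the same way in both arms. Enrolment is a safer basis than date of arrival, because the article does not say that the early enumeration recorded when households moved in. The downside is a smaller sensitivity set, which also loses households that were resident but not enrolled before randomisation.
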